## Abstract

**Background:**

Heart failure (HF) is a significant public health concern. Early detection, particularly during the asymptomatic stage, is essential for prompt intervention and preventing progression. Conventional measures, such as left ventricular ejection fraction (LVEF) have limited sensitivity. However, left ventricular global longitudinal strain (GLS) can detect subclinical myocardial dysfunction. Preliminary data from the previous HERZCHECK study showed that 23% (1023/4509) of participants in rural Germany had GLS-defined subclinical pre-HF (stage B HF) when examined with mobile cardiac MRI units. Yet, the prevalence of asymptomatic HF in urban populations remains unclear. The WE-CARE-HF-CMR trial aims to address this issue.

**Conclusion:**

The WE-CARE-HF-CMR trial will provide critical data on the prevalence of subclinical pre-HF (stage B HF) in urban populations. Using CMR-based GLS analysis with stationary and mobile units, and building on the HERZCHECK trial methodology, the study will close the diagnostic gap between rural and urban areas. These findings may ultimately support the implementation of targeted screening programs for subclinical pre-HF (stage B HF) to enable early intervention and prevent the progression to symptomatic HF.

**ClinicalTrials.gov Identifier:**

NCT07185100

## Background

1

Heart failure (HF) is a significant public health concern worldwide. In Germany, the prevalence of clinically overt HF is greater than 30 cases per 1000 people, resulting in an associated annual healthcare cost of €25,532 per patient [1], [2]. Due to the increase in life expectancy and the higher incidence of HF among elderly people, many more individuals are at risk of developing HF in the future [3]. Individuals with established cardiovascular risk factors are particularly at risk. For example, obesity and elevated blood pressure have been linked to a ∼45% relative increase in the residual lifetime risk for HF [3]. Therefore, it is essential to detect the early asymptomatic phase of HF, particularly within this high-risk group.

Subclinical pre-HF, or stage B HF, is defined as the presence of structural or functional cardiac abnormalities without symptoms [4]. Individuals with subclinical pre-HF (stage B HF) are at an increased risk of progressing to clinically manifest (i.e., symptomatic) HF [5]. However, conventional parameters such as left ventricular ejection fraction (LVEF) have limited ability to detect early myocardial dysfunction in asymptomatic individuals [6]. Left ventricular global longitudinal strain (GLS) describes the change in myocardial length from end-diastole to end-systole in the longitudinal plane and can be assessed by echocardiography or CMR. It has emerged as a promising parameter for detecting subclinical myocardial impairment without LVEF impairment [7], [8].

The recently completed HERZCHECK study (NCT05122793) screened the population of German rural regions for early subclinical pre-HF (stage B HF) using mobile cardiac magnetic resonance imaging (MRI) units [9]. These units were centrally coordinated and telemedically supervised by an expert core center. HERZCHECK was the first initiative to collect validated, multimodal data, including imaging, biospecimens, and patient-reported outcomes, from a large enough cohort of 4509 patients in medically underserved rural areas. Preliminary data from this cohort indicates a 23% (1023/4509) prevalence of subclinical pre-HF (stage B HF) and the study successfully demonstrated the feasibility of large-scale mobile cardiac magnetic resonance (CMR) screening [10].

Although symptomatic HF is known to be more prevalent in rural areas, it is unclear whether the prevalence of subclinical pre-HF (stage B HF) is comparable between urban and rural populations with equivalent risk profiles. This is due to differences in lifestyle, environmental exposure, and infrastructure [11]. Access to healthcare is more limited and income levels are lower in rural regions compared to urban areas, whereas the urban population is exposed to higher levels of air and noise pollution [12]. Therefore, it is necessary to extend the established HERZCHECK trial methodology to an urban setting.

The WE-CARE-HF-CMR study, built on the HERZCHECK trial, was designed to assess the prevalence of subclinical pre-HF (stage B HF) in urban populations using a standardized CMR-based approach that includes both stationary and mobile imaging units.

## Study design and methodology

2

### Overview of study design

2.1

The WE-CARE-HF-CMR study is a single-center prospective observational study with a cross-sectional baseline assessment and an exploratory longitudinal follow-up. The objective is to determine the prevalence of subclinical pre-HF (stage B HF) in urban areas of Germany. Data will be collected in five major cities (Berlin, Cologne, Frankfurt, Hamburg, and Munich), each with a population of at least one million, using stationary and mobile cardiac MRI (Fig. 1). The results will be benchmarked against the rural prevalence data obtained from the HERZCHECK study [9].

**Fig. 1 fig0005:**
[figure not shown]
Overview of the WE-CARE-HF-CMR study design, including eligibility criteria, study locations, and study examination. *CMR* cardiovascular magnetic resonance

### Ethics

2.2

The WE-CARE-HF-CMR trial has been approved by the Ethics Committee of Charité – Universitätsmedizin Berlin in Germany (application number EA4/166/25) and has been registered with ClinicalTrials.gov (NCT07185100). The study is conducted in accordance with the Declaration of Helsinki and Good Clinical Practice guidelines. Written informed consent will be obtained from all participants.

### Study population, screening, and enrollment

2.3

The WE-CARE-HF-CMR study enrolls asymptomatic individuals who reside in urban areas and have one or more of the following risk factors, but no known heart failure: hypercholesterolemia, arterial hypertension, obesity, smoking/tobacco consumption, chronic diabetes mellitus, and/or chronic kidney disease (CKD). The inclusion and exclusion criteria are largely identical to those of the previous study, except for the following points: for this study, individuals do not need to have existing health insurance or access to a smartphone [9]. Participants are referred by outpatient and occupational physicians, or can enroll themselves. All participants are screened for eligibility by a physician on the day of the examination.

### Study examinations

2.4

All participants receive a standardized diagnostic work-up identical to that of the HERZCHECK trial, including medical history, laboratory testing, CMR, and quality of life (QoL) questionnaires [9].

#### Medical history

2.4.1

The on-site physicians of the study center or remote telemedicine providers collect a focused medical history of the participants using the same questionnaire as in the HERZCHECK trial [9].

#### Laboratory testing

2.4.2

A venous blood draw is performed, collecting a total of two ethylenediaminetetraacetic acid tubes and one serum tube of blood. Participants also submit a urine sample to examine the urinary albumin creatinine ratio (UACR). All blood and urine samples are analyzed in the Deutsches Herzzentrum der Charité laboratory at the Campus Virchow Klinikum in Berlin, Germany. The examined laboratory parameters match those of the HERZCHECK trial protocol, except that C-reactive protein was added to the panel, and electrolytes were removed [9].

#### Quality of life questionnaires

2.4.3

The “HeartQoL” and the “PROMIS®-29 Profile” questionnaires, adopted from the HERZCHECK trial, are used to assess quality of life. To assess therapy adherence, the “MARS-10” questionnaire was also added [9]. Participants complete the questionnaires by themselves.

#### Cardiovascular magnetic resonance imaging and image analysis

2.4.4

The contrast-free CMR protocol and image acquisition procedure are adopted from the HERZCHECK trial. The central imaging parameter used to assess cardiac function is still the left ventricular GLS, which is quantified using a feature-tracking approach [9]. Newly added components include the fast strain-encoded imaging (fSENC) sequences in long- and short-axis views, and a lung water imaging sequence (Fig. 2) [13], [14], [15]. Mapping data are not used for diagnosis of subclinical pre-HF (stage B HF), but are acquired for exploratory and future analysis. The acquired images are transferred to the study center for offline analysis using CVI42 version 6.3.1 (Circle Cardiovascular Imaging Inc., Calgary, Alberta, Canada). The analysis follows the current consensus recommendations for the standardized image interpretation and post-processing [16]. All personnel were trained at the CMR-Academy of the Deutsches Herzzentrum der Charité (CMR-Academy, Deutsches Herzzentrum der Charité, Berlin, Germany) and all study investigators are certified according to the Society of Cardiovascular Magnetic Resonance (SCMR) regulations. Structured reports were generated using Centricity Cardio Workflow version 7.0 (GE HealthCare Technologies Inc, Chicago, Illinois).

**Fig. 2 fig0010:**
[figure not shown]
Overview of the CMR protocol used in the WE-CARE-HF-CMR trial. Similar to the previous HERZCHECK trial, no contrast- or stress-agents are administered, and it includes a survey, cine imaging, native T1 and T2 mapping. Newly added components are fSENC sequences in short- and long-axis views as well as lung water imaging sequences. *CMR* cardiac magnetic resonance, *fSENC* fast strain-encoded imaging

### Diagnostic reporting

2.5

All participants receive a comprehensive report containing their CMR and laboratory results. This report will include information about their left ventricular GLS and other relevant findings. The report also includes recommendations for guideline-compliant pharmacotherapy, risk factor modifications, and lifestyle optimizations. In case of clinically relevant incidental findings, participants are informed and referred to appropriate specialist care.

### Stratification and study endpoints

2.6

In accordance with the 2022 American Heart Association (AHA) guidelines for the management of HF and using previously established cutoffs of the left ventricular GLS, all participants will be categorized as healthy (GLS < −15%) or pre-HF (GLS ≥ −15%) [4], [17]. The primary endpoint of this study is the prevalence of subclinical pre-HF (stage B HF) in an urban population. Secondary endpoints include therapy adherence and the range of quality of life among individuals with subclinical pre-HF (stage B HF) in urban Germany and the prevalence of CKD. CKD is defined as an estimated glomerular filtration of < 60 mL/min at the time of the study visit.

### Statistical considerations

2.7

The primary objective is to determine the prevalence of subclinical pre-HF (stage B HF) in an urban population. With a target sample size of 450 participants and assuming that the true prevalence is similar to that in rural areas (23%, [1023/4509], preliminary data) [10], we can determine the prevalence of subclinical pre-HF (stage B HF) with an accuracy of up to 4 percentage points (half-width of the 95% confidence interval). To accurately assess the preventive impact, we plan to analyze data from 450 participants over an additional 10-year follow-up period. To account for a potential dropout rate of about 25% (including non-analyzable CMR images due to artifacts and losses to follow-up), we aim to enroll a total of approximately 600 participants. We will perform the statistical analysis to determine the prevalence of subclinical pre-HF (stage B HF), similarly to the method used in the HERZCHECK trial [9]. Study data is collected and managed using REDCap electronic data capture tools hosted at Charité – Universitätsmedizin Berlin, Germany [18], [19].

### Follow-up

2.8

The long-term effects of the preventive measures and therapy recommendations will be assessed during a 10-year follow-up period. To this end, patients will undergo re-evaluations at the one-, five-, and ten-year marks to assess their health status and QoL using questionnaires.

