The data from the HERZCHECK and the WE-CARE-HF-CMR trial together have the potential to enhance future patient care and guide the development of management strategies for this patient cohort. Additionally, the resulting large-scale quantitative database containing multimodal data (imaging, biomarkers, and structured QoL assessments) would facilitate the study of intra-individual progression of HF.

Several limitations should be acknowledged. First, the use of GLS ≥ −15% as the sole criterion for subclinical pre-HF (stage B HF) represents a simplification of the 2022 AHA/ACC definition, which encompasses a broader range of structural and functional abnormalities. This pragmatic approach was chosen to ensure methodological consistency with HERZCHECK and cross-platform reproducibility in a screening context. Second, participant recruitment through both physician referral and self-enrollment may introduce selection bias, as self-enrolling individuals in urban areas may differ systematically from the general at-risk population in terms of health awareness and socioeconomic status. Third, while the use of both mobile and stationary MRI units is a strength for logistical flexibility, potential scanner-related differences in GLS quantification should be considered, although cine-derived feature tracking is less susceptible to such variability than parametric mapping. Finally, the study is limited to five German cities and may not be generalizable to other urban populations with different demographic compositions.

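### The 10-year follow-up is said to assess preventive impact, but a single cohort in which everyone is advised cannot identify an effect of the preventive measures at any sample size

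*Protocol article*

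**What the plan says.** Two sentences in the protocol article claim an effect of an intervention.

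- Statistical considerations (2.7): "To accurately assess the preventive impact, we plan to analyze data from 450 participants over an additional 10-year follow-up period".
- Follow-up (2.8): "The long-term effects of the preventive measures and therapy recommendations will be assessed during a 10-year follow-up period".

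The intervention is the individual report. Diagnostic reporting (2.5) says "All participants receive a comprehensive report containing their CMR and laboratory results", and then "The report also includes recommendations for guideline-compliant pharmacotherapy, risk factor modifications, and lifestyle optimizations".

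The means of assessment are also in section 2.8: "re-evaluations at the one-, five-, and ten-year marks to assess their health status and QoL using questionnaires".

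Overview of study design (2.1) describes a "single-center prospective observational study with a cross-sectional baseline assessment and an exploratory longitudinal follow-up". Its only outside reference is HERZCHECK: "The results will be benchmarked against the rural prevalence data obtained from the HERZCHECK study". The endpoints in section 2.6 are pre-HF prevalence, therapy adherence, quality of life and CKD prevalence. Incident heart failure, change in GLS and preventive impact are not among them.

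**The concern.** An effect is a contrast between what happened under the measures and what would have happened without them. The article describes no group, internal or external, that shows the second state. A change in health status or quality of life over ten years in this cohort would combine any effect of the advice with ten years of ageing, changes in routine care over the decade, and selective loss of less healthy participants.

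At stake is how the 10-year data will be read. The current wording invites a stable or improved course to be reported as a benefit of screening and advice, and a decline as a failure of it. Neither reading would be supported. Pairing the claim with 450 participants and the word *accurately* suggests that the sample was sized for this purpose, which it was not.

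**Working it through.** **1. Inputs from Statistical considerations (2.7).** Assumed prevalence 23% (1023/4509 = 22.7%); 450 analysed; 95% interval half-width of up to 4 percentage points; dropout about 25%; about 600 enrolled.

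**2. Reproducing the plan's own figures.**

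- Wald half-width = 1.96 × √(p(1 − p)/n) = 1.96 × √(0.23 × 0.77/450) = 0.0389, or 3.89 points.
- Wilson gives 3.88 points. Clopper-Pearson with 104 of 450 gives 19.3% to 27.3%, a half-width of 4.00 points.
- The n for exactly 4 points is 1.96² × 0.23 × 0.77/0.04² = 425.2, so 426.
- Enrolment: 450/(1 − 0.25) = 600.

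All stated figures reproduce. The 450 follows from the precision of a baseline proportion. The 600 adds one allowance for unreadable scans and loss to follow-up together. No effect size, event rate, comparator or power for preventive impact enters either number.

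**3. What the follow-up can estimate.** Let τ be the average effect of the report and recommendations on a follow-up outcome, and let b be everything else that shifts the outcome over ten years (ageing, changes in care, selective retention). Because section 2.5 gives the report to everyone, the observed mean change D satisfies

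D → τ + b as n grows.

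This is one equation with two unknowns. The standard error of D shrinks with n, but b does not. Going from 450 to 600, or to any larger number, gives a more precise estimate of τ + b and no information that separates the two.

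**4. Contrasts that might be used instead.**

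| Contrast | Why it does not give τ |
|---|---|
| Before versus after in the whole cohort | Estimates τ + b, as in step 3 |
| Pre-HF (about 450 × 0.23 = 103.5, so 104) versus the other 346 | Both groups receive the report, so the difference is prognostic |
| WE-CARE-HF-CMR versus HERZCHECK | Section 2.1 uses HERZCHECK for baseline prevalence only; no follow-up comparison is stated |
| Adherent versus non-adherent participants | Not stated as an analysis; people who adhere differ in other ways, and the contrast concerns adherence, not the giving of advice |

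**5. Outcome against aim.** Section 2.6 defines pre-HF by CMR-derived GLS. Section 2.8 introduces the 1-, 5- and 10-year contacts as the means to assess the long-term effects, and the stated instrument is questionnaires. Under that follow-up the GLS-defined state is measured once, at baseline, and its change is not observed.

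**6. Label against claim.** Section 2.1 and the abstract call the follow-up exploratory, whereas section 2.7 says it will assess preventive impact accurately. Both cannot describe the same component.

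**The case against.** The strongest reply is that these are two loosely worded sentences about a component the article itself calls exploratory. The objective in section 2.1 and the primary objective in section 2.7 are both the prevalence, and preventive impact is not an endpoint. That stands as to scale: the primary result is untouched. It does not remove the point. Exploratory status weakens the strength of an inference but does not supply a comparator, and it conflicts with *accurately*. A later analysis plan cannot repair this either, since section 2.5 leaves nobody unadvised. The four limitations in the Discussion (GLS as sole criterion, selection, scanner differences, generalisability) do not include the missing comparator.

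Several stronger readings are tempting, and the article does not support them:

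- **That the sample size is wrong or was inflated for the prevention aim.** Deleting the preventive-impact sentence leaves 450 and its derivation unchanged. Loss to follow-up is part of the 25% allowance, but no effect size is.
- **That the study cannot show any progression to heart failure.** A health-status questionnaire could record a self-reported diagnosis or admission. Only change in the GLS-defined state is clearly unobserved under the stated follow-up.
- **That adherence or uptake of the advice is not collected.** Section 2.8 names domains, not items. Section 2.4.3 adds MARS-10, and adherence is a secondary endpoint. Item content, and whether MARS-10 is repeated, are details an article may leave to the full protocol.
- **That the Discussion promises repeat imaging.** Its remark that the combined HERZCHECK and WE-CARE-HF-CMR database "would facilitate the study of intra-individual progression of HF" is a conditional outlook, not a planned measurement.
- **That the problem can be sized by expected heart-failure events.** That needs a progression rate the article does not give, and the point holds for any rate.

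**Conclusion.** The concern holds as a mismatch between a stated aim and the stated design. Sections 2.7 and 2.8 claim to assess an effect of the preventive measures, and the design described in sections 2.1, 2.5 and 2.8 cannot identify one. The size of the resulting bias cannot be given: it equals b in the working, which the data cannot separate from the effect, and it does not diminish with n. The 450 supports a baseline prevalence to within about 3.9 points at 23% and nothing about prevention.

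This rests on two assumptions: that the full protocol adds no comparator that the article leaves out, and that follow-up is by questionnaire as section 2.8 states. If repeat CMR were planned, the remark on GLS-defined change would fall, but the lack of identification would remain. No stated number is wrong, and the prevalence estimate is not affected.

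**What to change.** - **Sections 2.7 and 2.8:** replace the preventive-impact and long-term-effects wording with a descriptive and prognostic aim. For example: the follow-up will describe the course of self-reported health status and quality of life at 1, 5 and 10 years, and their association with baseline GLS category, as an exploratory analysis.
- **Section 2.7:** state that 450 rests only on the precision of the baseline prevalence, and that the 25% allowance leads from 450 to 600.
- **Discussion, limitations:** add that all participants receive the report and recommendations and that there is no comparator, so no causal effect of screening or of the recommendations can be inferred from the follow-up.

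The changes are to wording only: sample size, visits, measurements and the primary analysis stay as they are. The cost is a less ambitious stated aim for the follow-up. If the sponsor wishes to keep a claim about effect, the article would have to name a comparator and an outcome suited to it, which is a different design.

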## Discussion

3

This study describes a standardized, CMR-based approach for identifying the early, asymptomatic stages of HF in an urban population. The goal of early detection is to enable timely interventions that prevent progression to symptomatic HF, reduce mortality, and maintain patients’ quality of life.

After completing the HERZCHECK trial, which focused on rural regions and excluded urban areas, we identified the need to address this gap. The WE-CARE-HF-CMR trial is designed to provide a complete national picture. A previous study showed that the rural population is 40% more likely to suffer from clinically manifest HF than the population in big urban municipalities [11]. Therefore, it is all the more important not to draw conclusions from one setting to another.

We are applying an already tested and proven approach from the previous trial by adapting the HERZCHECK protocol to the urban population. GLS was selected as the primary screening parameter because it detects subclinical myocardial dysfunction before a decline in LVEF becomes apparent, and has demonstrated strong independent prognostic value for adverse cardiovascular outcomes [20], [21]. CMR-derived GLS can be measured quickly and reproducibly from long-axis cine images, with excellent intra- and inter-observer agreement, and remains assessable even in the presence of image artifacts [22], [23]. We acknowledge that GLS alone does not capture all components of subclinical pre-HF (stage B HF) as defined by current guidelines, particularly structural changes such as diffuse myocardial fibrosis detectable by T1 mapping. However, in a population-level screening setting using both mobile and stationary CMR platforms, cine-derived GLS offers superior cross-platform reproducibility compared to parametric mapping, which remains highly dependent on scanner hardware, field strength, and sequence implementation. The pragmatic choice of a single, well-validated functional parameter reflects the screening nature of this study. Following the original protocol ensures methodological consistency, enabling the opportunity to investigate potential differences in subclinical pre-HF (stage B HF) prevalence between urban and rural regions. Furthermore, CMR is a diagnostic method known for its high reproducibility and low operator dependency, and GLS is a robust parameter with good intra- and inter-observer variability, which helps control for confounding factors related to image acquisition and analysis [22], [23], [24].

Using mobile MRI units overseen by the Deutsches Herzzentrum der Charité (Berlin) enables large-scale, centralized quality-controlled screening. This approach was essential for providing advanced cardiac diagnostics in underserved rural regions during the HERZCHECK trial. In urban areas, while access is less constrained, the mobility of the units offers critical logistical benefits of flexibility and scalability. Thus, the WE-CARE-HF-CMR trial methodology is a feasible model for large-scale screening of subclinical HF. Additionally, deploying mobile MRI units ensures methodological comparability to the HERZCHECK trial.

The data from the HERZCHECK and the WE-CARE-HF-CMR trial together have the potential to enhance future patient care and guide the development of management strategies for this patient cohort. Additionally, the resulting large-scale quantitative database containing multimodal data (imaging, biomarkers, and structured QoL assessments) would facilitate the study of intra-individual progression of HF.

Several limitations should be acknowledged. First, the use of GLS ≥ −15% as the sole criterion for subclinical pre-HF (stage B HF) represents a simplification of the 2022 AHA/ACC definition, which encompasses a broader range of structural and functional abnormalities. This pragmatic approach was chosen to ensure methodological consistency with HERZCHECK and cross-platform reproducibility in a screening context. Second, participant recruitment through both physician referral and self-enrollment may introduce selection bias, as self-enrolling individuals in urban areas may differ systematically from the general at-risk population in terms of health awareness and socioeconomic status. Third, while the use of both mobile and stationary MRI units is a strength for logistical flexibility, potential scanner-related differences in GLS quantification should be considered, although cine-derived feature tracking is less susceptible to such variability than parametric mapping. Finally, the study is limited to five German cities and may not be generalizable to other urban populations with different demographic compositions.

